# Remission effect of Canagliflozin in patients with newly diagnosed type 2 diabetes mellitus: a protocol for a multicenter, parallel-group, randomized, controlled, open-label trial

**DOI:** 10.1186/s12902-023-01461-9

**Published:** 2023-10-10

**Keywords:** Canagliflozin, Type 2 diabetes mellitus, Remission, Metformin, Sodium-glucose cotransporter-2 inhibitor

## Abstract

**Background:**

Studies reporting the effects of metabolic surgery, lifestyle intervention, and intensive insulin therapy for the remission of type 2 diabetes (T2DM) has been increasing, with fruitful results better conducted and yielded. However, there are only a few studies on the remission of T2DM using oral hypoglycemic drugs. Therefore, this study aims to investigate the remission effect of canagliflozin and metformin on participants with newly diagnosed T2DM and its possible underlying mechanism(s) through which these two medications elicit diabetes remission.

**Method:**

To this end, we performed a multicenter, parallel-group, randomized, controlled, and open-label trial. A total of 184 participants with a ≤ 3-year course of T2DM will be enrolled and randomly assigned to the canagliflozin or metformin treatment group in a ratio of 1:1. Participants in each group will maintain their medication for 3 months after achieving the target blood glucose level and then stop it. These participants will be followed up for one year to determine remission rates in both groups.

**Discussion:**

In this study, we will establish that whether canagliflozin is superior to metformin in terms of remission rate in participants with newly diagnosed T2DM. The results of this trial may provide robust evidence regarding the efficacy and mechanisms of the action of sodium-glucose cotransporter-2 inhibitors (SGLT2is) in T2DM remission.

**Trial registration:**

ChiCTR2100043770(February 28, 2021).

**Supplementary Information:**

The online version contains supplementary material available at 10.1186/s12902-023-01461-9.

## Background

Increasing evidence has shown that it is possible to remit type 2 diabetes mellitus (T2DM) [1, 2]. Currently, three main methods are effective for remitting T2DM. Metabolic surgery is the most efficacious, with a maximum remission rate of approximately 70–80% at 1–2 years after surgery [3, 4], followed by lifestyle interventions with caloric restriction, with a 40–80% average remission rate at 1 year after intervention [5], and intensive insulin therapy, which can also provide remission in 30–70% of patients with T2DM [6, 7]. The most commonly used oral hypoglycemic agents for the treatment of T2DM have been understudied to date. There are relatively many studies on pioglitazone in remitting T2DM [8], and relevant studies have shown that pioglitazone can prolong the remission of T2DM, whereas gliclazide has a poor remission effect on T2DM [9]. Although metformin is the first-line drug for the treatment of T2DM, studies on its remission of T2DM are scarce, and only a few have published its use in combination with other drugs for T2DM remission [10]. A national diabetes cohort study from the United Kingdom reported that patients with a disease course of < 2 years and glycosylated hemoglobin A1c (HbA1c) level of < 7.0% had a greater probability of remission with metformin alone or no hypoglycemic drugs and a ≥ 10% reduction in body mass index (BMI) [11]. In addition, a study found that short-term intensive insulin therapy was not more effective than metformin therapy in newly diagnosed patients [12]. According to these studies, metformin is beneficial for remission in patients with newly diagnosed T2DM.

The mechanism through which metabolic surgery and lifestyle intervention initiate T2DM remission is mainly based on [name] “double vicious circle theory” [13]. Through weight loss, patients can remove excess fat load, reduce body fat content to below the “personal fat threshold”, improve liver and pancreas fat deposition, thus improving insulin resistance, and make de-differentiated islet cells re-differentiate into insulin-producing β-cells; taken together, all these effects lead to T2DM remission. Intensive insulin therapy alleviates T2DM by reducing blood glucose concentrations and improving glucose toxicity, lipotoxicity, proinsulin toxicity, proamylin toxicity, and cytokine toxicity. In recent years, new drugs have been used to treat diabetes clinically. Sodium-glucose cotransporter-2 inhibitors (SGLT2is) have attracted considerable attention because of their significant hypoglycemic effect and extensive clinical efficacy. Canagliflozin, a SGLT2i, is a new targeted oral glucose-lowering drug that inhibits the reabsorption of urine glucose sodium-dependent glucose transporter 2 in proximal renal tubular epithelial cells and increases the excretion of glucose in the urine. Specifically, it plays a hypoglycemic role through non-insulin-dependent mechanisms, thus, reducing blood glucose effectively and safely [14, 15]. In addition, SGLT2i improves insulin resistance and protects β-cell function [16]. This class of drugs not only reduces glucose levels but also causes weight loss, improves insulin resistance, and protects β-cell function while having multiple effects on the reversal and remission of T2DM [16]. Therefore, we hypothesized that canagliflozin could be effective for T2DM remission. Existing studies on the remission of T2DM have found that the shorter the course of the disease, the greater the probability of remission [17–19]; therefore, active intervention at the onset of diabetes is conducive to increasing the probability of remission. Based on this, we plan to select participants with a ≤ 3-year course of T2DM as the study subjects, and give them canagliflozin or metformin treatment to explore whether these two drugs are conducive to the remission of type 2 diabetes.

In recent years, the prevalence of diabetes has risen sharp [20, 21], which causes great physiological [22, 23], psychological [24, 25] and economic [21] harm to patients. After achieving the remission of diabetes through relevant measures, the life quality of patients can be improved, the incidence of complications and concomitant diseases can be reduced [26], the physical and mental health of patients is benefited, and the economic burden of families as well as society is reduced. Therefore, research and implementation of the remission of type 2 diabetes are particularly important, which are also the objectives of this study.

### Study objectives

The primary objectives are to assess the effects of canagliflozin and metformin on diabetes remission and determine whether canagliflozin is superior to metformin. The secondary objective is to explore the possible underlying mechanisms by which the two medications elicit T2DM remission.

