### Sample size calculation

This is a controlled trial aims at exploring the remission effect of canagliflozin on T2DM. The experimental group is the canagliflozin group, and the control group is the metformin group. The main observation index is the remission rate. We referred to relevant studies and set the remission rate for metformin as 20.9%, similarly the estimated remission rate of canagliflozin was also 20.9%. For non-inferiority design, the cut-off value was 2%, α = 0.025, and power = 0.80. The sample size calculated by PASS 15 software was 73 cases in each group, and at least 92 participants should be enrolled in each group at baseline, for a total of 184 participants.

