### Data analysis

All statistical analyses will be performed by full-time statisticians using R Studio (Version 1.2.5001, R Studio Inc., Boston, MA, USA). The normality test will be used to determine whether the data are normally distributed. Continuous variables with a normal distribution will be reported as the mean ± SD, and ordinal and non-normally distributed variables will be reported as the median and interquartile range. Independent samples t-tests or Mann-Whitney U-tests will be used for comparisons, as appropriate. Categorical variables will be reported as counts and proportions, and the Pearson χ^2^ test or Fisher’s exact test will be used for comparisons, as appropriate.

The primary outcomes (remission rate 3 months after drug withdrawal and after 1 year of follow-up) will be compared between groups using Pearson’s χ^2^ test or Fisher’s exact test. Logistic regression will be used to adjust for potential confounders. Variables with P < 0.05 in the univariate comparisons, and known confounders that could impact the efficacy, will be included in the multivariable logistic regression models.

Subgroup analyses will be conducted of the primary outcomes stratified by age group (young, 18 ~ 35 years; middle-aged, 36 ~ 59 years; older, 60 ~ 65 years); duration of disease (<1 year, 1 ~ 2 years, 2 ~ 3 years); BMI (18.5 ~ 27.9 kg/m^2^, 28 ~ 40 kg/m^2^); and sex, using the same methods of analysis.

For the secondary outcomes, continuous data will be analyzed using the linear mixed effects model, which will use the random intercept model to explain the internal correlation of participants. Discontinuous data will be analyzed similar, but the generalized linear model appropriate to the distribution assumptions and link functions will be used. The analysis of all secondary outcome indicators also corrected for potential confounders (including variables with P < 0.05 in the univariate comparisons and known confounders that could have an impact on the efficacy). The safety indicators will be analyzed using the same methods used to analyze the main outcome indicators.

Missing values will be filled using multiple imputation methods, and sensitivity analyses will be performed.

Two-tailed P-values will be used, and P-values < 0.05 will be regarded as statistically significant. Point estimates will be reported with 95% confidence intervals.

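### The trial asks and tests superiority but is sized for non-inferiority at equal rates, so its 80% power does not belong to the planned primary comparison

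*Protocol article*

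**What the plan says.** Three parts of the protocol article bear on the primary hypothesis.

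- **Question.** Study objectives sets out to "determine whether canagliflozin is superior to metformin". The Discussion paragraph of the Abstract repeats it: the trial is to establish "whether canagliflozin is superior to metformin in terms of remission rate".
- **Sample size.** Sample size calculation uses a different hypothesis: "For non-inferiority design, the cut-off value was 2%, α = 0.025, and power = 0.80". It says the investigators "set the remission rate for metformin as 20.9%, similarly the estimated remission rate of canagliflozin was also 20.9" per cent, so the assumed difference is zero. The result: "The sample size calculated by PASS 15 software was 73 cases in each group", raised so that "at least 92 participants should be enrolled in each group at baseline, for a total of 184 participants".
- **Analysis.** Data analysis states "The primary outcomes (remission rate 3 months after drug withdrawal and after 1 year of follow-up) will be compared between groups" by Pearson's chi-square or Fisher's exact test, two-tailed, with significance at P < 0.05. Point estimates are to carry 95% confidence intervals. The section gives no margin, no rule comparing a confidence limit with a margin, and no sequence from non-inferiority to superiority.

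**The concern.** The objective and the test agree with each other, and the sample size calculation agrees with neither. A chi-square or Fisher test has equality as its null hypothesis, so rejecting it shows a difference. Failing to reject it does not show that canagliflozin is no worse by more than a margin. The primary analysis therefore cannot confirm the hypothesis used for sizing, and the trial was not sized for the hypothesis it tests.

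Two things are at stake. A reader will take 80% as the chance of answering the stated question, when no superiority effect was ever assumed. And without a declared hypothesis and decision rule, a non-significant result in an open-label trial is open to being presented as similarity between the drugs.

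**Working it through.** **Inputs from the article.** Remission 20.9% in both groups; cut-off 2%; alpha 0.025, read as one-sided; power 0.80; 73 evaluable and 92 enrolled per group; 1:1 allocation; analysis at two-sided 0.05. The loss rate behind 92 is not stated, but 73/0.8 = 91.25, which rounds up to 92, so 20% is implied. Results are given for both 73 and 92. The canagliflozin rates other than 20.9% used below are assumptions to show a range, since the article gives no superiority effect.

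**Step 1. The plan's own figure.** For non-inferiority with equal rates p and margin d,

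n per group = (z₀.₉₇₅ + z₀.₈₀)² × 2p(1−p) / d²

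= 7.849 × (2 × 0.209 × 0.791) / 0.02² = 7.849 × 0.3306 / 0.0004 ≈ 6,488.

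The stated 73 is not reproduced. A Farrington-Manning calculation gives 6,491, a continuity correction 6,588, and one-sided alpha 0.05 gives 5,111. With 73 per group, the standard error at equal rates is √(0.3306/73) = 0.0673, so power at a 2-point margin is Φ(0.02/0.0673 − 1.96) = Φ(−1.66) ≈ 4.8% (5.2% with 92). The formula returns 73 at a margin of 18.9 points. Since 18.9 = 20.9 − 2.0, the 2% may have been entered as a remission rate rather than as a margin, but that is inference. The 80% is thus unsupported for the non-inferiority question as written too.

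**Step 2. The planned test at the planning rates.** Enumerating all pairs of binomial counts at 20.9% v 20.9%, the chi-square test is significant in favour of canagliflozin with probability 2.48% at both 73 and 92 per group. This is simply one tail of the type I error. It shows that the 80% does not carry over to superiority.

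**Step 3. What the sample can detect for superiority.** With p₁ = 0.209, p₂ the canagliflozin rate and p̄ their mean,

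power = Φ{ [ |p₂ − p₁| − 1.96 √(2p̄(1−p̄)/n) ] / √([p₁(1−p₁) + p₂(1−p₂)]/n) }.

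Example, n = 73 and p₂ = 0.423: p̄ = 0.316, null SE 0.0770, alternative SE 0.0749, so power = Φ[(0.214 − 0.1508)/0.0749] = Φ(0.84) ≈ 80%.

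| Assumed canagliflozin rate | Power, n = 73 | Power, n = 92 |
|---|---|---|
| 30.0% | 24% | 29% |
| 35.0% | 48% | 57% |
| 40.9% (+20 points) | 75% | 84% |
| Rate giving 80% power | 42.3% (+21.4 points) | 39.8% (+18.9 points) |

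**Step 4. What a non-significant result would mean.** At true rates of 10.9% on canagliflozin and 20.9% on metformin, enumeration gives significance against canagliflozin in 38.4% of trials with 73 per group and 46.0% with 92. The test would be non-significant in about 62% and 54% of trials, although remission had fallen by nearly half.

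**The case against.** **The confidence interval could serve.** Data analysis promises 95% intervals, and a two-sided 95% interval matches one-sided alpha 0.025. An analysis plan that is not shown could hold the rule comparing the limit with a margin. This limits the claim to what the article states. It does not remove the conflict: the article does fix the primary test and significance rule, and they belong to a different hypothesis from the one sized. No analysis plan can make Study objectives and Sample size calculation state the same hypothesis.

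**Non-inferiority followed by superiority is a recognised structure.** It is, but the article does not describe it. It would not rescue this sample either, because 73 per group has about 5% power at the stated margin.

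**The reading of a null result as equivalence is speculative.** Nothing in the article says it will be read that way. That is fair, so it is a risk to close off rather than a stated intention.

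**The 80% in the restated sensitivity is itself conditional.** It applies to one chi-square test at 0.05. With Fisher's exact test, power at the same detectable rates is about 75%. If alpha were split equally over the two primary time points (an assumption), the detectable rates would rise to 44.6% (n = 73) and 41.8% (n = 92). Both points stand and belong in the restated text.

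**A detectable difference is not a justification.** No passage supports a gain of 19 to 21 points. This stands as well, and is a reason to state the figure openly.

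**Conclusion.** The concern holds. Objective and test are superiority; the sample size is non-inferiority at equal rates; the article tests no non-inferiority hypothesis. The stated 80% does not describe the chance of answering the trial's own question. For superiority at two-sided 0.05 against 20.9%, the sample has 80% power only if canagliflozin roughly doubles remission, to about 40% to 42%. At a true 30% it has 24% to 29%.

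These figures rest on the article's 20.9% for metformin, on 73 to 92 analysed per group, and on a single chi-square test. The separate failure to reproduce 73 from the stated inputs means that rewording the objective as non-inferiority would not repair the plan. This should be corrected before the trial is analysed.

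**What to change.** 1. In Study objectives and Sample size calculation, declare superiority of canagliflozin the single primary hypothesis, in line with the Abstract and Data analysis. Remove the non-inferiority sentence, and record that its inputs do not yield 73.
2. Replace it with the sensitivity of the existing sample: 92 randomised and 73 evaluable per group give 80% power, two-sided 0.05, for 20.9% versus about 40% (if 92 are analysed) to 42% (if 73 are). Say that this is per test and for the chi-square test.
3. Make the remission-rate difference with its 95% confidence interval the primary result.
4. State that a non-significant test will not be called non-inferiority or equivalence.

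The cost is wording in the protocol and the analysis plan, with no extra patients. The detectable difference of about 19 to 21 points will look less favourable than the present text. If the sponsor cannot defend an effect of that size, the text should say so. For scale, by the same method, gains of 10, 15 and 20 points need 301, 141 and 83 evaluable per group, or 377, 177 and 104 enrolled at 20% loss.

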## Methods and analysis

### Study design

This is a multicenter, parallel-group, randomized controlled, open-label trial (Fig. 1). The study has been approved by the Medical Ethics Committee of the Jiangsu Hospital of Integrated Traditional Chinese and Western Medicine and registered in the Chinese Clinical Trial Registry (ChiCTR2100043770). This study will be conducted at Jiangsu Hospital of Integrated Traditional Chinese and Western Medicine, Suzhou Hospital of Traditional Chinese Medicine, Suqian Hospital affiliated with Xuzhou Medical University, Xuzhou Mineral Group General Hospital, Xiamen Hospital of Traditional Chinese Medicine, and Nanjing Jiangning District People’s Hospital. A total of 184 participants will be enrolled and randomly assigned to the canagliflozin and metformin treatment groups.

**Fig. 1 Fig1:**
[figure not shown]
Participant flow diagram

### Participants

#### Inclusion criteria (during screening, all six criteria must be met)

18–65 years old.No limitation on sex.Onset of T2DM (≤ 3-year course of the disease), diet and physical exercise alone for more than 8 weeks, and at least 8 weeks of no anti-diabetes medication (except short-term use for < 7 days).18.5 kg/m^2^ ≤ BMI ≤ 40 kg/m^2^.6.5% ≤ HbA1c ≤ 10%.Able to understand the procedures and methods of this study, willing to complete the study in strict compliance with the clinical trial guidelines, and voluntarily signing informed consent.

#### Exclusion criteria (during screening, those who meet any of these criteria will be excluded)

(1) Severe diabetic complications include severe diabetic nephropathy (estimated glomerular filtration rate (eGFR) of < 60 mL/min/1.73 m^2^), diabetic foot (Wagner grade 2 or above) and diabetic retinopathy (with fundus hemorrhage affecting vision).

(2) Severe organ diseases or other severe primary diseases such as liver and kidney dysfunction, heart failure, cerebral infarction, and malignant tumors.

(3) Severe cognitive dysfunction and unclear language expressions.

(4) Mental illness.

(5) Severe chronic infection.

(6) History of acquired immunodeficiency syndrome and drug abuse.

(7) Pregnant or lactating women.

(8) Participation in another clinical trial.

(9) Blood donation or blood loss of ≥ 400 mL within 4 weeks before screening or recipient of blood transfusion.

(10) Fasting plasma/serum glucose > 15 mmol/L.

(11) Alanine aminotransferase ≥ 2.5 × upper limit of normal(ULN).

(12) Total bilirubin ≥ 1.5 × ULN.

(13) Hemoglobin ≤ 100 g/L and neutrophils < 1.5 × 10^9^/L.

(14) Renal injury (eGFR < 60 mL/min/1.73 m^2^ or serum creatinine ≥ 2.5 × ULN or on kidney dialysis).

(15) Blood thyroid-stimulating hormone level beyond the normal range and has clinical significance, as assessed by researchers.

(16) Parathyroid hormone > 1.5 × ULN.

(17) Myocardial enzyme spectrum (creatine kinase and creatine kinase isoenzyme ck-mb) > 3 × ULN.

(18) Fasting triglyceride ≥ 5.64 mmol/L (500 mg/dL).

(19) Blood amylase and lipase levels exceed the upper limit of the normal range and are clinically significant, according to the researchers’ assessment.

(20) Other factors and laboratory outliers of clinical significance that the investigators believe may interfere with interpreting the efficacy and safety data in this study.

#### Exit and withdrawal criteria

(1) Pregnant women or women planning for pregnancy.

(2) Intolerable adverse events.

(3) Worsening of blood glucose levels.

(4) Severe or repeated hypoglycemia.

(5) Pancreatitis.

(6) Participants who do not take medication nor accept testing as required.

(7) Participants who cannot complete the study as planned or have other factors that may affect the efficacy or safety evaluation.

(8) Participants who participate in other clinical trials during the trial.

(9) Participants who voluntarily withdraw from the study with informed consent.

(10) Participants who do not explicitly raise the request to withdraw from the test but no longer accept medication, testing, and follow-up.

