### Randomisation and interventions

A total of 184 participants will be randomly allocated to receive either canagliflozin or metformin treatment (1:1). The randomization operation will be generated by an independent statistician, who will ensure the balance of participants according to age, sex, HbA1c and BMI and course of their disease when grouping, and a code list will be directly allocated to the main investigators of every center. The intervention content of the two groups is as follows.

Canagliflozin treatment group: For oral treatment, the participants will receive canagliflozin tablets (Janssen-Cilag S.p.A., Ltd., National Drug Approval: H20170375) once daily, 100–300 mg per time, with a minimum dose of 100 mg per day and maximum dose of 300 mg per day.Metformin treatment group: For oral treatment, the participants will receive metformin hydrochloride tablets (Sino-American Shanghai Squibb Pharmaceutical Co., Ltd., National Drug Approval: H20023370 (0.5 g × 20 tablets)/Sino-American Shanghai Squibb Pharmaceutical Co., Ltd., National Drug Approval: H20023371 (0.85 g × 10 tablets × 2 plates)), 1–3 times a day, 500–2000 mg per time, with a minimum dose of 500 mg per day and maximum dose of 2550 mg per day.

Regarding weekly titration for oral drug metering, the titration targets are fasting blood glucose (FBG) (3.9–5.6 mmol/L) and blood glucose at 2 h after each of the three meals (5.0–7.0 mmol/L). After meeting the above criteria, the participants will continue the medication for 3 months and then stop.

Routine diabetes health education will be provided to all participants during the treatment period. Routine diet control and appropriate exercises will be planned. Follow-up will be conducted monthly for the first 3 months after the end of treatment and every 3 months thereafter for 1 year (Table 1; Fig. 2). Participants with FBG > 7.0 mmol/L and postprandial blood glucose (PBG) > 10 mmol/L during the follow-up period are defined as having hyperglycemia recurrence, which will be treated according to the Chinese guidelines for the diagnosis and treatment of T2DM and is defined as not remitted.

**Table 1 Tab1:** Participant visit schedule

**Research Stage**	**Screening**	**Baseline**	**Intervention Period**				**Follow-up Period**		

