### Outcomes

#### Primary outcome

Remission rates.

This is the percentage of participants in each group who meet the remission criteria during follow-up: HbA1c < 6.5% maintained for > 3 months after the treatment discontinuation [27].

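### The exit list does not separate stopping the study drug from leaving the trial, so people who stop early may lose a primary outcome that is in any case measured off drug

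*Protocol article*

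**What the plan says.** The section Exit and withdrawal criteria is a single numbered list. Item 2 is "Intolerable adverse events" and item 4 is "Severe or repeated hypoglycemia". Item 6 is "Participants who do not take medication nor accept testing as required". The same list holds departures from the study itself: joining another trial (item 8), "Participants who voluntarily withdraw from the study with informed consent" (item 9), and silently ceasing to accept drug, tests and follow-up (item 10).

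The Primary outcome section defines remission as "HbA1c < 6.5% maintained for > 3 months after the treatment discontinuation". Randomisation and interventions starts follow-up once the glucose targets have been met and three further months of drug completed. Under Follow-up visit, contact after drug withdrawal is monthly by telephone, with a return to the centre every three months. For hyperglycaemia that recurs during follow-up, Randomisation and interventions adds "which will be treated according to the Chinese guidelines for the diagnosis and treatment of T2DM and is defined as not remitted". On missing data, Data analysis says "Missing values will be filled using multiple imputation methods, and sensitivity analyses will be performed".

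**The concern.** Items 2 and 4 are reasons for which a person may stop a drug. Standing beside items 8 to 10, they read as reasons to leave the trial, and no section describes a participant who is off drug but still followed. The follow-up schedule is written for the planned stop only.

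This matters more here than in most trials because everyone is meant to stop the drug and be observed without it. A participant who stops early can be observed in the same way, on visits that already exist. If the list is followed as written, that observation is not made, and no later analysis plan can recover HbA1c values that were never collected.

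The trial is open-label, and the two drugs have different dose ranges and are titrated weekly to set glucose targets. Tolerability and hypoglycaemia may therefore differ by arm, and the allocation is known when an event is judged intolerable. If exits differ by arm and those who exit would remit at a different rate from those who stay, the between-arm comparison is no longer fully protected by randomisation.

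**Working it through.** **1. The text.**
- Exit list: items 2 and 4 (drug-related events) and items 8 to 10 (leaving the study) have the same status.
- Primary outcome: needs HbA1c after discontinuation, whether or not treatment was completed.
- Randomisation and interventions, and Follow-up visit: both describe follow-up after the planned end of treatment. Neither mentions an early stop.
- Result: the outcome is measurable after an early stop, but nothing provides for measuring it.

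**2. The planned loss.** Sample size calculation gives 73 per arm, raised to 92, without stating a dropout rate. 73 / (1 − 0.20) = 91.25, rounded up to 92, so the step matches a 20% allowance. The loss allowed for is 92 − 73 = 19 per arm, and 19/92 = 20.7%. This covers every cause of loss, not only items 2 and 4. (How the 73 was reached is a separate matter, and nothing here rests on it.)

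**3. What imputation would have to assume.** If people who exit during treatment under items 2 and 4 have no off-drug HbA1c, their outcomes must be imputed from participants who stayed. If the model contains nothing that predicts both exit and remission, the imputed rate in an arm equals, in expectation, the rate among those observed in that arm.

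Take the same true remission rate in both arms, p = 20.9% (the article's planning value), exit share e, and remission q among exits. The observed rate is then (p − e·q)/(1 − e). **The values of e and q are assumptions; the documents give none.**

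| Exits, arm A v arm B | q | Observed A | Observed B | Spurious difference |
|---|---|---|---|---|
| 20% v 20% | 0% | 26.1% | 26.1% | 0 |
| 25% v 15% | 0% | 27.9% | 24.6% | 3.3 points |
| 25% v 15% | 5% | 26.2% | 23.7% | 2.5 points |
| 25% v 15% | 10% | 24.5% | 22.8% | 1.7 points |
| 25% v 15% | 20.9% | 20.9% | 20.9% | 0 |
| 30% v 10% | 0% | 29.9% | 23.2% | 6.6 points |
| 30% v 10% | 10% | 25.6% | 22.1% | 3.5 points |

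First 25% v 15% row: 0.209/0.75 = 0.2787 and 0.209/0.85 = 0.2459, difference 0.0328. Swapping the arms reverses the sign. With equal exits and equal q, or with exits who remit like everyone else, there is no bias.

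**4. Scale.** With 92 per arm at 20.9%, the standard error of the difference is √(2 × 0.209 × 0.791 / 92) = 0.060, or 6.0 points. The 25% v 15% cases are roughly 0.3 to 0.5 of a standard error; 30% v 10% with no remission among exits is about 1.1.

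**The case against.** The list never says that data collection ends after items 2 or 4, and a full protocol behind the article might provide for it. That is fair as to certainty: the text shown is open to more than one reading. But it does state a rule on who exits, places these events among study departures, and offers no other status.

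Several stronger readings are tempting, and the documents do not support them.

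- **That the analysis rests on completers.** It does not; multiple imputation and sensitivity analyses are planned. The remaining problem is that the imputation assumption cannot be checked. The table shows a limiting case, and useful predictors could reduce the bias.
- **That missing doses alone forces exit under item 6.** Its wording joins drug and testing and can mean refusal of both. Someone who refuses testing cannot be measured, so that loss would not be avoidable. Items 2 and 4 carry the point without it.
- **That no one who exits has any off-drug HbA1c.** The list is not limited to the treatment period, and an exit during follow-up may come after such a measurement.
- **That one drug is favoured.** No exit rates by arm are given.
- **That the bias can be judged against the 2% margin.** The exit rates are assumed, and Data analysis describes two-tailed tests without a margin.

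One objection stands in full. A person who stops early may start another glucose-lowering treatment, and HbA1c on that treatment is not the off-drug outcome. Keeping the visits is therefore not enough without a rule for counting such people.

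**Conclusion.** The point holds as a weakness that is cheap to repair. Followed as written, the exit list would lose the primary outcome of people who stop drug for intolerance or hypoglycaemia, although that outcome could still be measured. Imputation would then protect the comparison only if exits resemble those who stayed, given the variables in the model.

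Size and direction are unknown. Under the assumed values the spurious difference runs from 0 to 6.6 points. It requires exits, or remission among exits, to differ between arms. The 20.7% allowance bounds the planned loss from all causes and says nothing about its split by cause or arm.

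The exit for "Worsening of blood glucose levels" in the same list is a related but separate matter: it has to be reconciled with the rule that recurrence in follow-up counts as not remitted.

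**What to change.** Change the wording of Exit and withdrawal criteria and the matching outcome text:

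1. Divide the list into stopping study drug, and withdrawing consent or being lost to follow-up.
2. State that participants in the first group stay in the already scheduled HbA1c visits, with time counted from their actual last dose, and are analysed in their randomised arm.
3. State how participants who start other glucose-lowering treatment after an early stop count for remission, consistently with the not-remitted rule in Randomisation and interventions.
4. Clarify that item 6 ends study participation only when testing is also refused.

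This concerns data collection and analysis only. It changes no dose and no clinical rule for stopping treatment. The cost is an edit to the protocol and continued contact with participants who are off study drug, at visits that are already planned. In return, up to 19 more participants per arm (92 rather than 73) could have an observed outcome, though those who withdraw consent or are lost will still be missing.
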